## Abstract

**Background:**

Opioid use disorder (OUD) among women delivering at a hospital has increased 400% from 1999–2014 in the United States. From the years 2007 to 2016, opioid-related mortality during pregnancy increased over 200%, and drug-overdose deaths made up nearly 10% of all pregnancy-associated mortality in 2016 in the US. Disproportionately higher rates of neonatal opioid withdrawal syndrome (NOWS) have been reported in rural areas of the country, suggesting that perinatal OUD is a pressing issue among these communities. There is an urgent need for comprehensive, evidence-based treatment services for pregnant women experiencing OUD. The purpose of this article is to describe a study protocol aimed at developing and evaluating a perinatal OUD curriculum, enhancing evidence-based perinatal OUD treatment in a rural setting, and evaluating the implementation of such collaborative care for perinatal OUD.

**Methods:**

This two-year study employed a one group, repeated measures, hybrid type-1 effectiveness-implementation design. This study delivered interventions at 2 levels, both targeting improvement of care for pregnant women with OUD. The first area of focus was at the *community healthcare provider-level*, which aimed to evaluate the acceptability and feasibility of perinatal OUD education across time and to improve provider education by increasing knowledge specific to: MOUD provision; screening, brief intervention, and referral to treatment (SBIRT) utilization; and NOWS treatment. The second area of intervention focus was at the *patient-level*, which assessed the preliminary effect of perinatal OUD provider education in promoting illicit opioid abstinence and treatment engagement among pregnant women with OUD. We adopted constructs from the Consolidated Framework for Implementation Research (CFIR) to assess contextual factors that may influence implementation, and the Reach, Effectiveness, Adoption, Implementation, and Maintenance (RE-AIM) model to comprehensively evaluate implementation outcomes.

**Discussion:**

This article presents the protocol of an implementation study that is employing the CFIR and RE-AIM frameworks to implement and evaluate a perinatal OUD education and service coordination program in two rural counties. This protocol could serve as a model for clinicians and researchers seeking to implement improvements in perinatal care for women with OUD in other rural communities.

*Trial registration* NCT04448015 clinicaltrials.gov.

## Background

Opioid use disorder (OUD) among women delivering at a hospital has increased 400% from 1999–2014 in the United States [1] From the years 2007 to 2016, opioid-related mortality during pregnancy increased over 200%, and drug-overdose deaths made up nearly 10% of all pregnancy-associated mortality in 2016 in the US [2]. Access to care and lack of provider understanding of evidence-based treatment for perinatal OUD are both contributing factors to drug-related pregnancy-associated and pregnancy-related deaths, particularly in rural areas [3, 4]. Disproportionately high occurrences of neonatal opioid withdrawal syndrome (NOWS) have been reported in rural areas of the country, suggesting that perinatal OUD is a critical issue among rural communities [5].

Without treatment, maternal OUD is associated with adverse perinatal outcomes including increased risk of preterm delivery, low birth weight and difficulty breastfeeding [6–10] Undertreatment of maternal OUD also increases risk of maternal return to use, overdose and death [3, 11]. Effective treatment is available for maternal OUD during pregnancy—specifically medication for opioid use disorder (MOUD) and psychosocial services [12]. Maternal treatment for OUD is associated with significant benefits to both the mother and infant [12–15] There is an urgent need for comprehensive, evidence-based OUD treatment services specifically for pregnant women experiencing this disorder. OUD is a chronic disease and will persist beyond pregnancy; the focus of this study is addressing the specific treatment gap evident for women experiencing simultaneous OUD while pregnant and/or postpartum (i.e. perinatal OUD).

### Barriers to implementation in rural areas

Rates of maternal opioid use and NOWS in rural areas have climbed substantially over the past ten years compared to their urban counterparts [16], yet treatment engagement among this population has failed to keep pace [17], While the effectiveness of MOUD in treating OUD is well-established, [13] the limited availability of buprenorphine (BUP) prescribers and methadone clinics in rural areas has created a substantial barrier to accessing these life-saving treatments for those with OUD—including pregnant women [18, 19]. Within rural areas, buprenorphine prescribers frequently do not treat pregnant patients [20]. Indeed, mothers with OUD and their infants living in rural areas frequently require transfer to other hospitals following delivery to receive high-level, specialty substance use and neonatal care [21]. Perceptions of OUD as a moral failing among pregnant women have given rise to punitive approaches rather than evidence-based medical care [22]. Rural prescribers also identify stigma from other providers as a major barrier to providing MOUD [23]. Lack of specialty support for complex problems, such as perinatal OUD, also creates a significant barrier to rural healthcare providers offering MOUD [24]. As of 2017, 60.1% of rural counties did not have a buprenorphine-waivered physician [25].

Substantial gaps exist for pregnant women with OUD receiving evidence-based care, and this is particularly true in rural America. Presently, little research is available regarding implementation of evidence-based services for these women. It is critical to identify replicable and sustainable approaches to implement needed OUD care for this vulnerable population. This article presents the protocol of an implementation study that is employing the Consolidated Framework for Implementation Research (CFIR) [26] and the Reach, Effectiveness, Adoption, Implementation, and Maintenance (RE-AIM) [27] framework to implement and evaluate a perinatal OUD education and service coordination program in two rural Utah counties. The CFIR serves to assess contextual factors at the beginning and throughout the project that may influence implementation success, while the RE-AIM functions as a post-implementation framework to assess implementation outcomes. This protocol could serve as a model for clinicians and researchers seeking to implement improvements in perinatal care for women with OUD in rural communities. The purpose of this project is to describe a study protocol aimed at developing and evaluating a perinatal OUD curriculum, enhancing evidence-based perinatal OUD treatment in a rural setting, and evaluating the implementation of such collaborative care for perinatal OUD.

## Methods

### Design

This two-year study is employing a one group, repeated measures, hybrid type-1 effectiveness-implementation design, [28] which emphasizes clinical effectiveness monitoring while also gathering information regarding the implementation of the program. This study delivers interventions at 2 levels, both targeting improvement of care for pregnant women with OUD. The first area of focus is at the *community healthcare provider-level*, which aims to evaluate the acceptability and feasibility of perinatal OUD education across time and to improve provider education by increasing knowledge specific to: MOUD provision; screening, brief intervention, and referral to treatment (SBIRT) utilization; and NOWS treatment. The second area of intervention focus is at the *patient-level*, which assesses the preliminary effect of perinatal OUD provider education in promoting illicit opioid abstinence and treatment engagement among pregnant women with OUD. The research team is interested in assessing changes across time among recipients. Time and resources necessary to implement an experimental or quasi-experimental design are not available for this project. For this reason, the research team has chosen to utilize a single arm design. The University of Utah Institutional Review Board approved this study.

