#### Participant assessments

Women who have provided consent are asked to complete a baseline assessment prior to receiving the intervention. This assessment consists of a series of self-report and interviewer administered questionnaires regarding health, mental health, social service involvement, and substance use. These constructs were selected for assessment given that the interventions and services provided to participants were anticipated to have an impact on these areas. Two follow-up assessments are collected: a pre-delivery follow-up at 34 to 40 weeks of gestation and a post-delivery follow-up 30 days following delivery. These assessments contain the same questionnaires as the baseline assessment, with the exception of the Adverse Childhood Experience scale since these scores are related to childhood experiences and therefore should not vary over the course of the study. We are also collecting data from the woman’s and her infant’s medical records (Table 4). In addition, our team will work with the local department of health to obtain county level data across time at the conclusion of the project to assess intervention impact within the larger community (Table 4). In the event that a participant chooses to discontinue their participation in the study, no additional data will be collected from that participant.

**Table 4 Tab4:** Patient-level study measures

Source	Outcome	Domain	Instrument	Source of data	Baseline	Pre-delivery follow-up	Post-delivery follow-up
Health department	Hepatitis B Virus (HBV)	Health	ICD10 Code B16	Health department	X		X
	Hepatitis C Virus (HCV)	Health	ICD10 Code B18.2	Health department	X		X
	Human Immunodeficiency Virus (HIV)	Health	ICD10 Code B20	Health department	X		X
	Syphilis	Health	ICD10 Code A53.9	Health department	X		X
	Gonorrhea	Health	ICD10 Code A54.9	Health department	X		X
	Chlamydia	Health	ICD10 Code A74.9	Health department	X		X
	Child welfare involvement	Social	ICD10 Code Z62.21	Health department	X		X
	Overdose	Health	ICD10 Cod T40.6	Health department	X		X
Medical record	Pre-eclampsia	Health	ICD10 Code O14	Medical record			X
	Pre-term birth	Health	ICD10 Code O60	Medical record			X
	Cesarean section	Health	ICD10 Code O82;	Medical record			X
	Intrauterine growth restriction	Health	ICD10 Code P05.9	Medical record			X
	Birth weight	Health	ICD10 Code P07	Medical record			X
	Apgar score	Health	ICD10 Code P09	Medical record			X

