#### Resource enrichment

In addition to improved provider knowledge and skills through the education portion of this intervention, women who participate in this study receive enriched perinatal care. A nurse care manager hired through the project and embedded in the local women’s health clinic provides care coordination for participants. Nurse care management services involve activities such as regular follow-up with enrolled women between appointments in order to promote ongoing engagement in care; resource identification, referral, and enrollment assistance with relevant resources, such as mental health care, support groups, and social services.

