## Limitations

While this study has several strengths including its focus on implementation of evidence-based care, targeting an underserved population within rural communities, and the inclusion of providers, its limitations should be discussed. This implementation intervention was designed for a specific rural community, which could potentially limit generalizability of the findings; however, rural counties across the US appear to be experiencing similar challenges, [5] and this intervention may be adapted for site-specific needs. This study is a single arm trial with no control group, and therefore evaluation through an implementation framework, like RE-AIM, is critical in adequately assessing the study’s effect on intervention effectiveness, uptake and sustainability.

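### The patient-level aim credits provider education with changes that a single-arm study of education plus nurse care management cannot assign to either component

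*Protocol article*

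**What the plan says.** All places are in the protocol article.

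- **Aim.** In Design, the second focus is the patient level, "which assesses the preliminary effect of perinatal OUD provider education in promoting illicit opioid abstinence and treatment engagement among pregnant women with OUD". The Methods paragraph of the Abstract says the same. Neither sentence mentions care management.
- **Design.** One group with repeated measures. The reason given is that "Time and resources necessary to implement an experimental or quasi-experimental design are not available for this project".
- **What women receive.** Resource enrichment states: "In addition to improved provider knowledge and skills through the education portion of this intervention, women who participate in this study receive enriched perinatal care". It continues: "A nurse care manager hired through the project and embedded in the local women’s health clinic provides care coordination for participants". The listed tasks include contact between appointments so that women stay in care.
- **Baseline.** Under Participant assessments, consenting women are "asked to complete a baseline assessment prior to receiving the intervention". Which component that means is not said. Needs assessment and implementation evaluation starts patient data at each woman's own enrolment. Follow-ups are at 34 to 40 weeks of gestation and 30 days after delivery.
- **Timing of education.** Provider assessments and Provider education report the kick-off training and introductory lectures in the past tense, with monthly sessions continuing. Participants describes recruitment of women as in progress. No date is given for the kick-off or for the first enrolment.
- **Analysis.** t-tests and chi-square tests across time points, with no subgroup or interim analyses.
- **Limitations.** The section admits a single arm without a control group and concludes that "evaluation through an implementation framework, like RE-AIM, is critical in adequately assessing" how well the programme works, is taken up and lasts.

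**The concern.** The aim names one cause, but the women are exposed to two, and the second acts directly on one of the two named outcomes. Admitting that there is no control group does not cover this. That admission concerns whether the programme as a whole had an effect; the aim goes further and says which part of the programme produced it. The inference in Limitations adds to the difficulty, because it offers an evaluation framework as the answer to a missing comparison.

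At stake is what the final report may conclude. If the aim is followed literally, any improvement from baseline is reported as a preliminary effect of educating providers. The article presents itself as a model for other rural communities, so the component that receives the credit matters to its readers.

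**Working it through.** The article states no sample size, power or effect size, so there is no figure to reproduce. The check is whether the planned data can yield the effect that the aim names.

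**Step 1: write down one woman's change.** Let *t* be the effect of time (the course of pregnancy and delivery), *e* the effect of provider education and *c* the effect of nurse care management. Let *f* be the share of the education effect that begins after her baseline, between 0 and 1. Then

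change from baseline = *t* + *f* × *e* + *c*.

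Care management is coded as absent at baseline and present afterwards, for every woman, from Resource enrichment and Participant assessments.

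**Step 2: count what can be estimated (education coded on/off).**

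| Enrolment | *f* | Expected change | Independent equations, of 3 unknowns | Is *e* estimable? |
|---|---|---|---|---|
| All before kick-off | 1 | *t* + *e* + *c* | 1 | No |
| All after kick-off | 0 | *t* + *c* | 1 | No |
| Some of each | 1 and 0 | both of the above | 2 | Only as the difference between the two groups |

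In the mixed case, (*t* + *e* + *c*) − (*t* + *c*) = *e*. This requires *t* and *c* to be equal in the earlier and later enrolees, and it is a subgroup contrast, which Analyses rules out. More women give a more precise estimate of the sum but do not separate its parts.

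**Step 3: put illustrative numbers in.** The effects are assumed, in percentage points of abstinence.

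| *e* | *c* | *t* | Change seen if *f* = 1 | Change seen if *f* = 0 |
|---|---|---|---|---|
| 0 | 20 | 0 | 0 + 20 + 0 = 20 | 20 + 0 = 20 |
| 20 | 0 | 0 | 20 + 0 + 0 = 20 | 0 + 0 = 0 |
| 0 | 0 | 20 | 0 + 0 + 20 = 20 | 0 + 20 = 20 |
| 10 | 10 | 0 | 10 + 10 + 0 = 20 | 10 + 0 = 10 |

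With a baseline before education (*f* = 1), all four situations look alike. With a baseline after education (*f* = 0), a real education effect of 20 disappears, while an effect of 20 from care management or from time alone would be credited to education.

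**Step 4: allow for continuing sessions.** Monthly teaching means that *f* may lie between 0 and 1. With *e* = 20 and *c* = *t* = 0, the change seen is 20 × *f*, anywhere from 0 to 20. Since *f* is not known, this adds an unknown and no equation.

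**Step 5: look for another source of comparison.** The county-level data listed under Participant assessments cover infections, overdoses and child welfare, not abstinence or engagement. The patient-care efficacy row of Table 2 uses the participants' own records and questionnaires and names no comparator. Neither isolates *e*.

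**The case against.** The strongest reply is that this is an openly uncontrolled pilot. The aim says preliminary, Design says the interest is in change over time among recipients, and no analysis of component effects is planned. The article also describes a package in several places: the Background speaks of education together with service coordination, the Discussion expects benefit from both parts, and the Conclusion names both. All of that is true, and it makes this a matter of one badly worded aim and its consequences. It does not remove the point: preliminary signals imprecision, not a shared cause, and the aim is the sentence against which the results will be reported.

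Several stronger readings are tempting, and the article does not support them.

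- *That every woman's baseline follows the education.* The tenses suggest it for women enrolled after the kick-off, but there are no dates, and sessions continue monthly. The baseline sentence can also already be read as before care management, since the article elsewhere calls the care manager's work an intervention.
- *That regression to the mean inflates the change by some stated amount.* Eligibility sets no severity threshold, so selection at a peak of use is undocumented and no size can be given.
- *That Table 2's efficacy question is wrong.* Its programme label plausibly includes care management, because another row counts use of care management among the programme's resources. It needs clarifying only.
- *That logged care-management contacts could separate the components.* Their number may well vary between women, but contact is likely to follow need, so such an analysis would be confounded.
- *That the single arm or the lack of a power calculation is at fault.* Both are disclosed and explained.

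**Conclusion.** The point holds for the aim in Design and the Abstract and for the inference in Limitations. The effect of provider education on abstinence and engagement cannot be estimated from the planned before-after tests at any sample size, because every enrolled woman also receives care management and moves through pregnancy over the same interval. This rests on Resource enrichment applying to all participants, as written, and on no unplanned contrast between enrolment cohorts being added.

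The baseline part is conditional. If women enrolled after the kick-off, their within-woman change would largely miss the effect of the introductory education; if they enrolled before it, the components remain mixed all the same. The main conclusion does not depend on which is the case.

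The size of any misattribution is unknown, since the article gives no effects; the 20-point figures only illustrate that it can run in either direction. This is a correction of wording and of the permitted conclusion. It does not invalidate the design, and no visit, measure or planned test has to change.

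**What to change.** 1. **Design and Abstract.** Restate the patient-level aim along these lines: *to describe within-woman change from enrolment in illicit opioid use and treatment engagement under the combined programme of provider education and nurse care management; change is not attributable to either component.* This agrees with how the Background already describes the programme.
2. **Participant assessments.** State that the intervention which baseline precedes is nurse care management.
3. **Table 2, efficacy row.** Make clear that the patient-care question concerns the combined programme.
4. **Limitations.** Replace the inference that RE-AIM makes up for the missing control group with a statement that before-after change does not isolate the programme's effect.

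The cost is a few sentences and a more modest claim. No added participants, data collection or analyses are needed.

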### Study setting

The study setting for this project is rural Utah. From 1999–2014, the proportion of women with OUD delivering at a hospital in Utah has increased nearly ten-fold [1]. Utah ranks among the highest nationally in terms of opioid overdose rates among women [29] and frequency of opioid prescribing to pregnant women insured by Medicaid (41.6%) [30]. The leading cause of deaths among pregnant and postpartum women in this state is drug-related, with 77% of these deaths involving opioids [3].

Two adjacent rural counties [31] in Utah were chosen as the target for the intervention, with a local women’s health clinic as the focal point of care. These counties were selected because of the high rates of opioid overdose, limited resources, and high degree of existing community engagement [32–34]. These two rural counties lead the state in rates of opioid overdose deaths, with collectively 47.7 per 100,000 compared to the state average of 17.4 deaths per 100,000 [32].

### Implementation framework

In order to accomplish our objectives, we are adopting constructs from the CFIR to assess contextual factors that may influence implementation [26]. We also are utilizing the RE-AIM model to efficiently and comprehensively evaluate implementation outcomes of the multilevel intervention [27].

Five domains characterize the CFIR: *intervention characteristics, outer setting, inner setting, characteristics of the individuals involved*, and *the process of implementation*. Within each domain, we have identified several constructs relating to the efficacy, sustainability and reproducibility of the intervention, and are using these constructs to guide the development and execution of the project (Table 1). We are assessing *intervention characteristics,* such as evidence strength and quality, complexity of the intervention, and relative advantage of the intervention to help guide the development and dissemination of our perinatal OUD education curriculum. Further, within the *inner setting*, the research team is examining structural characteristics at the healthcare provider level in order to improve our understanding of the climate and characteristics of the organizations that would be receiving the intervention. Also related to the *inner setting*, we are assessing *characteristics of individuals involved*, such as knowledge and beliefs about the intervention and individual stage of change, to inform the research team on how to make the education information more appealing to providers and support uptake by providers and patients. We also are engaging with community representatives to gain knowledge about *outer setting* components of the CFIR model, such as cosmopolitanism, in order to understand the degree to which local organizations are linked and work together. We are also working to assess patient needs and resources, as well as to understand knowledge of providers regarding barriers and facilitators for meeting patient needs. Finally, the *process of implementation* domain is guiding our understanding of the efforts of implementation leaders and champions during implementation preparation with respect to planning and engaging in the project.

**Table 1 Tab1:** Consolidated framework for implementation research targeted domains at the healthcare provider, patient advocate, and community representative levels

CFIR domain	CFIR construct	Level
Intervention characteristics	Evidence strength and quality	Healthcare provider level
	Complexity	Healthcare provider Patient advocate
	Relative advantage	Healthcare provider Patient advocate
Outer setting	Cosmopolitanism	Community Representative
	Peer pressure	Community Representative
	Patient needs and resources	Community Representative
Inner setting	Structural characteristics	Healthcare provider
	Readiness for implementation	Healthcare provider
	Implementation climate	Healthcare provider
Characteristics of individuals involved	Knowledge and beliefs about the intervention	Healthcare provider Patient Advocate
	Individual stage of change	Healthcare provider Patient advocate
Process of implementation	Planning	Healthcare provider Community representative Patient advocate
	Engaging	Healthcare provider Community representative Patient advocate
	Formally appointed internal implementation leaders	Healthcare provider
	Champions	Healthcare provider Patient advocate

The RE-AIM model is an effective tool for comprehensively evaluating multilevel interventions using five dimensions [27] (Table 2). Using this framework provides a streamlined way to assess the various components of an implementation project and the intervention itself, allowing our team to understand which components are facilitators or barriers of its overall success in a real-world environment. Specifically, we will use the *Reach* and *Adoption* aspects of this framework to assess uptake of the intervention, as operationalized in Table 2. We further will rely on the *Efficacy*, *Implementation,* and *Maintenance* components of RE-AIM to evaluate the success of the intervention and implementation strategy in educating healthcare providers over the course of the study and afterward, as described in Table 2. This evaluation approach maps on well with the hybrid effectiveness-implementation study design [27, 28].

**Table 2 Tab2:** RE-AIM Evaluation of Perinatal Addiction Education

Dimension and questions addressed	Data sources	Methods	Outcome/Process measures
Reach			
To what extent did perinatal addiction education reach the providers treating pregnant women with OUD in Your Counties?	Department of Professional Licensing	Identify all healthcare providers in the community licensed to potentially treat pregnant women with OUD	Number of community providers included in the study/ total number of community providers working with pregnant women with OUD
To what extent did perinatal addiction education reach the pregnant women with OUD within the healthcare system in Your Counties?	Local healthcare and social service agencies	Electronic medical records; health department records	Number of patient participants/ total number of pregnant women with opioid misuse in Your Counties during the study duration
Efficacy			
How effective was the provider training and support?	Community providers	Questionnaires assessing skills, knowledge and satisfaction	Mixed method surveys regarding provider experience and skillset
How effective were perinatal addiction education services in improving care for pregnant women with OUD?	Healthcare and social service records; patient participants	Compare data regarding illicit substance use, MOUD continuity, opioid poisoning occurrences, physical and mental health, and social service involvement; questionnaires to assess patient perception	Medical codes; standardized comprehensive wellness measurement instruments; qualitative surveys
Adoption			
To what extent are community providers using perinatal addiction education practices when treating patients with perinatal OUD?	Community providers; local healthcare agencies	Questionnaires assessing provider practices and attitudes; electronic medical records	Mixed methods surveys regarding provider practices; frequency of MOUD provision, NOWS treatment and SBIRT by participating community providers
To what extent are patients utilizing resources made available through the perinatal addiction education program?	Partnering agencies (e.g. EUWH, Four Corners Behavioral Health); medical records; pharmacy records	Interviews with partner agencies; electronic medical record and pharmacy record evaluation	Utilization of care management and resources made available through this project; number of MOUD prescriptions filled; presence of BUP in urinalysis via medical record
Implementation			
What were the barriers and facilitators of high quality care?	Community providers	Questionnaires and focus groups	Perceptions of and feedback regarding the implementation kickoff event, as well as ongoing training and support provided via the implementation of perinatal addiction education
Maintenance			
Will the perinatal addiction education practices be maintained over time in Your Counties?	Community providers; healthcare administrators	Interviews and questionnaires with community providers and healthcare administrators regarding provider practices and policies	Questionnaire regarding how integrated perinatal addiction education practices are into standard treatment of pregnant women with OUD and what policies exist to support them

*OUD* Opioid Use Disorder, *MOUD* Medication for Opioid Use Disorder, *NOWS*  Neonatal Opioid Withdrawal Syndrome, *SBIRT* Screening, Brief Intervention, and Referral to Treatment; *BUP* Buprenorphine

